### Cost-effectiveness analysis

We will conduct cost-effectiveness to examine both the costs and health outcomes of the concrete floor intervention. We will collect data on floor installation costs from a program perspective, separating material and labor costs, since in the future households may install floors themselves. Using an ingredients-based approach, we will record costs for individual line items within categories including capital costs, materials, transportation, personnel, and operations. We will then adapt our previously published natural history and cost-effectiveness models of childhood helminth infections and enteric fever to project the health impacts and cost-effectiveness of floor installation (Lo et al. 2016, 2018; Ryckman et al. 2021; Weyant et al. 2024). We will populate the model with outcome rates from the control and intervention arms of this trial, simulate age-specific risk over a ten-year period, and project DALYs for each health outcome for households with concrete floors and soil floors.

We will calculate DALYs for child STH infections, child diarrhea, child wasting, and maternal depression using published disability weights (Global Burden of Disease Collaborative Network/Institute for Health Metrics and Evaluation, n.d.). While we expect the intervention to influence a broad range of outcomes, disability weights are only available for the subset listed above. We will calculate disability weights for hookworm-associated anemia as the product of the disability weight for anemia due to hookworm disease by the probability that an individual infected with hookworm develops anemia (Bartsch et al. 2016). For each STH infection, we will estimate the probability of mild, moderate, and severe infections based on Ct values from qPCR using data from a prior study of children in rural Bangladesh (Benjamin-Chung et al. 2020). For diarrhea, we will calculate weights assuming the distribution of mild, moderate, and severe diarrhea is the same as found in the MAL-ED study in Bangladesh (Platts-Mills et al. 2015).

We will perform simulations under different scenarios for the durability of intervention effects and intervention coverage, adjusting for inflation. The model will predict costs and health outcomes, deaths, and DALYs averted over a 10-year period; we will obtain 95% credible intervals for uncertainty. We will estimate the incremental cost-effectiveness ratio for concrete vs. soil household floors. Parameter draws from variable distributions will be performed through Latin Hypercube Sampling (Stein 1987). We will perform a probabilistic sensitivity analysis with pre-specified ranges of key parameters (e.g., disability weights, costs, intervention effects) supported by our study findings and the literature (Blower and Dowlatabadi 1994; Basu and Andrews 2013). If we find that the cost of concrete floors made with the fly ash mix differs from that of traditional concrete floors, we will repeat the cost-effectiveness analysis specifically for green concrete floors using the same methods.

## Figures and Tables

**Figure 1. F1:**
[figure not shown]
Hypothesized mechanisms of intervention effects

**Figure 2. F2:**
[figure not shown]
Planned measurements in the CRADLE trial Intensive environmental samples collected at the 6-month follow-up include courtyard soil, floor soil, food, drinking water, chicken feces, cow feces.

**Figure 3. F3:**
[figure not shown]
CRADLE Study site map A) Map of study site location within Sirajganj and Tangail districts, Bangladesh. B) Exterior boundary of unions included in the study site in Chauhali, Belkuchi, and Nagarpur unions of Sirajganj and Tangail districts. Base map source: Esri.

**Table 1. T1:** Outcome measures

Primary outcome	
Prevalence of any soil-transmitted helminth using qPCR	Proportion of children in which *Ascaris lumbricoides, Necator americanus, or Trichuris trichiura* was detected in stool by qPCR at any follow-up measurement (6, 12, 18, or 24 months of age).
Secondary outcomes	
*Child health outcomes*	
Prevalence of *Ascaris lumbricoides, Necator americanus* or *Trichuris trichiura* using qPCR	Proportion of children in which *Ascaris lumbricoides, Necator americanus* or *Trichuris trichiura* was detected in stool by qPCR at any follow-up measurement (6, 12, 18, or 24 months of age).
Mean *Ascaris lumbricoides, Necator americanus* and *Trichuris trichiura* eggs per gram	Geometric and arithmetic mean of *Ascaris lumbricoides, Necator americanus* and *Trichuris trichiura* eggs per gram detected in stool by Kato-Katz at any follow-up measurement (6, 12, 18, or 24 months of age)
Diarrhea prevalence	Prevalence of caregiver-reported and stool consistency based child diarrhea in the past 7 days (at least three loose or watery stools within 24 hours or at least one bloody stool) at any follow-up measurement (6, 12, 18, or 24 months of age)
Relative abundance and diversity of human pathogens	Human pathogens detected in child stool using shotgun metagenomic sequencing each follow-up round
Relative abundance and diversity of antimicrobial resistance genes	Antimicrobial resistance genes detected in child stool using shotgun metagenomic sequencing each follow-up round
*Child behavior*	
Rate of child soil contact and ingestion	Mean number of soil contact and ingestion events per child-hour observed during 6-hour video observations at each follow-up (6, 12, 18, 24 months)
*Child development outcomes*	
Mean ASQi score at 12 and 24 months	Mean communication, fine motor, gross motor, problem solving, personal-social and combined scores measured using the Ages and Stages Inventory calculated separately at 12 months and 24 months
Mean overall Family Care Indicator score at 12 and 24 months	Mean Family Care Indicator score overall measured separately at 12 months and 24 months (range: 0-3)
*Maternal outcomes*	
Prevalence of stress (mild, moderate and severe)	Proportion of mothers with Perceived Stress Scale scores 0-13 (mild), 14-26 (moderate), 27-40 (severe) at 6 at 6 and 18 months
Prevalence of prenatal and postnatal depression	Proportion of mothers with Edinburgh Postnatal Depression scale score of 9.5 or higher at baseline and at 6 and 18 months
Prevalence of maternal satisfaction with quality of life, household floor quality and housing quality	Proportion of mothers reporting that they were “very satisfied”, “satisfied”, or “somewhat satisfied” with their quality of life, household floor quality and housing quality at each follow-up (6, 12, 18, 24 months)
Prevalence of improved maternal satisfaction with quality of life, household floor quality and housing quality	Proportion of mothers with an improvement in their reported quality of life, household floor quality and housing quality between baseline and each follow-up (6, 12, 18, 24 months)
Mean memory span	Mean length of consecutive blocks mothers correctly recalled (Corsi Span) using the Corsi Block Span task between baseline and follow-up at 3 and 12 months
Mean non-verbal reasoning score	Mean maternal Raven’s Progressive Matrices score between baseline and follow-up at 3 and 12 months
Mean maternal cognitive inhibition	Mean percentage of correct responses and response time in the Hearts and Flowers task at 6 and 18 months
Mean maternal cognitive flexibility and attention shifting	Mean percentage of correct responses and response time in the Dimensional Change Card Sort test at 7 and 18 months
Mean maternal daily discretionary time	Maternal time poverty using hybrid time diaries and activity lists that measure discretionary time use at 3 and 12 months
*Environmental outcomes*	
Prevalence of *Ascaris lumbricoides, Necator americanus*, and *Trichuris trichiura* in household floors	*Ascaris lumbricoides, Necator americanus*, and *Trichuris trichiura* detected by qPCR in household floor dust at any follow-up measurement (6, 12, 18, 24 months)
Prevalence of larvated *Ascaris lumbricoides* and *Trichuris trichiura* ova in household floors	Larvated *Ascaris lumbricoides* and *Trichuris trichiura* detected by microscopy in household floor swabs at any follow-up measurement (6, 12, 18, 24 months)
Most probable number of *E. coli* in household floor samples and child hand rinses	*E. coli* enumerated by IDEXX in household floor swabs and child hand rinses at any follow-up measurement (6, 12, 18, 24 months)
Most probable number of cefotaxime-resistant *E. coli* in household floor samples	Cefotaxime-resistant *E. coli* enumerated by IDEXX with cefotaxime supplement in household floor swabs at any follow-up measurement (6, 12, 18, 24 months)
Prevalence of extended-spectrum beta-lactamase producing *E. coli* (ESBL-E) and ESBL coding genes in household floor samples, courtyard soil, child hand rinses, drinking water, prepared food, cow feces and chicken feces	ESBL-E and ESBL coding genes in floor swabs, courtyard soil, child hand rinses, drinking water, prepared food, cow feces and chicken feces at 6 months follow-up
Mass of floor dust (g per m^2^)	Mass of dust on floors collected by sweeping a 2 m^2^ floor area next to bed where child sleeps at night (6, 12, 18, 24 months)
Relative abundance and diversity of human pathogens	Human pathogens detected in floor soil, cow feces and chicken feces samples using shotgun metagenomic sequencing each follow-up round
Relative abundance and diversity of antimicrobial resistance genes	Antimicrobial resistance genes detected in floor soil, cow feces and chicken feces samples using shotgun metagenomic sequencing each follow-up round
*Floor outcomes*	
Rate of floor sweeping and refinishing	Mean number of times floors were swept per household-day at each follow-up measurement and mean number of times floors were refinished per household-month at each follow-up measurement (6, 12, 18, 24 months)
Prevalence of holes or cracks in household floors	Proportion of household floors with holes or cracks at each follow-up measurement (6, 12, 18, 24 months)
Prevalence of impermeable household floors	Proportion of household floors in which surface water was still present after 1 minute at each follow-up measurement (6, 12, 18, 24 months)

**Table 2: T2:** Summary of variables measured in surveys

		Baseline	Birth	3 mo.	6 mo.	12 mo.	18 mo.	24 mo.
Household characteristics	Household construction materials	X			X	X	X	X
	Household census	X			X	X	X	X
	Household assets	X			X	X	X	X
	Parental education and employment	X			X			X
	WASH infrastructure & practices	X			X	X	X	X
	Animal ownership & husbandry	X			X	X	X	X
	Animal presence in the home	X			X	X	X	X
	Human and animal feces in the home	X			X	X	X	X
Perinatal outcomes	Prenatal and birth outcomes		X					
Anthropometry	Length, weight, head circumference	X	X	X	X	X	X	X
Illness symptoms	Child illness symptoms (e.g., diarrhea)	X			X	X	X	X
Flooring	Floor durability assessment	X			X	X	X	X
	Floor hygiene and maintenance	X			X	X	X	X
Child activities	Child motor skills				X	X	X	X
	Child cognitive development					X		X
	Child feeding practices				X	X	X	X
	Child play locations				X	X	X	X
Maternal outcomes	Quality of life	X		X		X		X
	Satisfaction with housing	X			X	X	X	X
	Perceived Stress Scale	X		X		X		
	Edinburgh Postnatal Depression Scale	X		X		X		
	Maternal bandwidth				X		X	
	Maternal time use			X		X		
Flooding status	Household flooding status	X			X	X	X	X
Water, sanitation, handwashing	Water storage, latrine access, child feces management, handwashing	X			X	X	X	X
Vaccination	Vaccination status of index child			X	X	X	X	X
Deworming and antimicrobials	Deworming status of household members	X			X	X	X	X
	Antimicrobial use of mother and index child	X			X	X	X	X
	Antimicrobial use in domestic animals	X			X	X	X	X
Food consumption	Animal milk consumption practices				X	X	X	
Environmental sampling	Environmental sample collection				X	X	X	X

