Installing finished floors, such as concrete, in homes with soil floors is a promising potential intervention to reduce child enteric infection. Concrete floors are easier to keep clean than soil floors, which may contribute to lower levels of fecal pathogens on surfaces, and subsequently on hands and fomites. Concrete may also interrupt the life cycle of STH, which require soil to reach their infective stage (S. Brooker, Clements, and Bundy 2006). A recent meta-analysis of observational studies estimated that the odds of any enteric or parasitic infection was 0.75 times lower and the odds of helminth infections was 0.68 times lower in homes with improved floors (e.g., concrete, wood) vs. unimproved floors (e.g., soil) (Legge, Pullan, and Sartorius 2023). In addition, studies have found protective associations between improved floors and diarrhea (Koyuncu et al. 2020; Cattaneo et al. 2009).

By making homes more comfortable and easier to keep clean, floor upgrades can also improve quality of life and reduce stress. A study in Mexico found that installing concrete floors was associated with 10.6% lower stress, 12.5% lower depression, and 18.7% higher satisfaction with quality of life among mothers (Cattaneo et al. 2009). Slum upgrades, including concrete or wood floor installation, have been found to improve sleep, quality of life, and happiness (Galiani et al. 2017; Simonelli et al. 2013). Though findings from these studies are promising, all prior research has been observational, and associations may be confounded by household wealth.

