### Statistical analysis

To assess randomisation, we will compare the means and percentages of baseline characteristics between arms including maternal age, maternal education level, paternal education, paternal employment, housing wall and roof materials, household assets, acres of homestead land owned, household WASH infrastructure and access, open defecation practices, and deworming in the prior 6 months, animal ownership, and animal cohabitation.

The primary analysis will compare prevalence of any STH between study arms using an indicator for whether a child tested positive at the 6, 12, 18, or 24 month follow-up rounds. We will estimate the unadjusted prevalence ratio comparing intervention to control using generalized estimating equations (Zeger, Liang, and Albert 1988) with a binomial family and log link and an exchangeable correlation matrix to account for repeated measures within the same child. If log-binomial models do not converge, we will use modified Poisson regression with robust standard errors (Zou 2004). Secondary analyses will include indicators for follow-up rounds in order to estimate the prevalence ratio at each follow-up to assess whether effects vary over different child ages. All models will condition on geographic block and estimate robust sandwich standard errors (Freedman 2006) to account for the matched design (McNutt et al. 2003; Kernan et al. 1999). To assess whether the intervention effect is sustained over 2 years, we will also fit a model with an interaction term between treatment and follow-up time.

We will also compare secondary outcomes (Table 1) between study arms. For repeated measures outcomes, we will use generalized estimating equations (Zeger, Liang, and Albert 1988) with an exchangeable correlation matrix; we will estimate mean differences for continuous outcomes using an identity link and Gaussian family and prevalence ratios for binary outcomes using a log link and binomial family (McNutt et al. 2003). For measurements analyzed at a single time point, we will fit generalized linear models (McNutt et al. 2003) with a Gaussian family and identity link for continuous outcomes and a binomial family and log link for binary outcomes. If log-binomial models do not converge, we will fit models with a Poisson and log link (McNutt et al. 2003; Zou 2004).

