Primary analyses will be unadjusted for covariates. A secondary analysis will adjust for baseline covariates to reduce bias associated with any chance imbalances between study arms at baseline and possibly increase efficiency (Pocock et al. 2002). We will pre-specify a potential covariate adjustment set of baseline variables and only adjust for covariates among this set that are associated with each outcome (likelihood ratio test p-value < 0.2).

Analyses will be intention-to-treat. The following households will be considered non-compliant: 1) control households that install concrete floors that cover at least one entire room inside the mother’s household; 2) households that cover at least one room’s floor with a cement finish; 3) intervention households that remove any part of the concrete floor installed as part of the trial; 4) intervention households in which a substantial portion of the concrete floor is damaged. If non-compliance exceeds 10% in either arm, we will perform a per-protocol analysis as well. We will not adjust for multiple comparisons because the number of outcomes is relatively modest, and the analysis will follow a pre-specified analysis plan.

We will compare attrition rates at each follow-up and across follow-ups between randomised arms and compare baseline characteristics of those lost to follow-up to those who complete the study. If there is evidence of systematic differences in attrition between arms and attrition exceeds 20%, we will explore whether study drop out resulted in selection bias using inverse probability of censoring weights with flexible machine-learning based estimation (Mark J. van der Laan 2011).

For STH measured in floor dust samples, the primary analysis will impute STH prevalence as 0 for floors that do not contain enough dust for nucleic acid extraction (0.1 g). The imputation assumes that floors with no dust do not harbor STH eggs. Our pilot data indicate that concrete floors in 40% of households may yield insufficient dust for nucleic acid extraction. We will conduct a secondary analysis by comparing STH outcomes in floor dust between intervention and control groups only using data from households where sufficient dust was obtained. We expect this analysis to yield a conservative estimate of intervention effectiveness because it will exclude intervention households with dust-free floors which are less likely to harbor STH eggs.

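### The maternal stress outcome uses bands that cover the entire Perceived Stress Scale and names no contrast or direction of benefit

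*Protocol article*

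**What the plan says.** Table 1 of the protocol article, under maternal outcomes, lists "Prevalence of stress (mild, moderate and severe") and defines it as "Proportion of mothers with Perceived Stress Scale scores 0-13 (mild), 14-26 (moderate), 27-40 (severe"). It gives no cut-off, no index band and no mean score for stress.

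The Statistical analysis section states: "We will also compare secondary outcomes (Table 1) between study arms". It provides mean differences for continuous outcomes and "prevalence ratios for binary outcomes using a log link and binomial family". It names no ordinal or multinomial model. On multiplicity it says: "We will not adjust for multiple comparisons because the number of outcomes is relatively modest".

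The next row of Table 1, on depression, is built differently, with a single threshold: "Proportion of mothers with Edinburgh Postnatal Depression scale score of 9.5 or higher".

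The Introduction sets the expected direction, that "floor upgrades can also improve quality of life and reduce stress", and cites an earlier study in Mexico in which "installing concrete floors was associated with 10.6% lower stress".

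**The concern.** A prevalence needs a group that counts as not having the condition, and this row has none. The reader must choose between pooling the bands, which gives a constant, and taking them one at a time, which gives three ratios with no statement of which one counts or which way benefit points. In the second case the label works against the reader, because a helpful intervention raises the prevalence of something called mild stress.

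The abstract names maternal stress among the secondary outcomes, and the trial has a directional hypothesis for it. The measure is self-reported by mothers who know their arm, and no multiplicity adjustment is planned. A choice of band, or a decision to collapse bands, made after the results are seen would therefore be hard to defend.

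**Working it through.** The document gives no mean, SD, prevalence or power for stress, so there is no stated figure to reproduce. Three checks follow.

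**1. Coverage.** The bands hold 14 scores (0-13), 13 scores (14-26) and 14 scores (27-40). That makes 41, which is every integer from 0 to 40, each in exactly one band. So mild + moderate + severe = 1 in each arm. Pooled, the prevalence ratio (PR) is 1.00/1.00 = 1 for any effect. Taken separately, any fall in moderate-plus-severe is matched by an equal rise in mild.

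**2. Direction of each band.** Assumptions, none from the document: normal scores truncated to 0-40, cut-points 13.5 and 26.5, mean 2 points lower with concrete floors.

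| Control mean, SD | PR mild | PR moderate | PR severe | PR for 14 or more |
|---|---|---|---|---|
| 14, 6 | 1.28 | 0.77 | 0.43 | 0.76 |
| 18, 7 | 1.38 | 0.92 | 0.60 | 0.87 |
| 22, 7 | 1.56 | 1.03 | 0.68 | 0.93 |
| 26, 6 | 2.14 | 1.20 | 0.73 | 0.98 |
| 30, 6 | 2.57 | 1.39 | 0.83 | 1.00 |

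Over means 14 to 30 and SD 6 and 7, the mild ratio is always above 1 (1.23 to 2.57) and the severe ratio always below 1 (0.43 to 0.85). The moderate ratio falls on either side of 1 (0.77 to 1.39), because that band gains mothers from severe and loses them to mild.

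**3. Power.** Inputs:
- 340 mothers per arm: 400 per arm less the 15% loss in the sample size section, 400 x 0.85 = 340. This assumes stress is measured in the full sample; it is not among the measures listed for subsamples.
- Control mean 18 and SD 6 (assumed).
- The 10.6% from the Introduction, read as a lower mean score (assumed): 18 x 0.106 = 1.908, so the intervention mean is 16.092.
- One visit, untruncated normal scores, two-sided 5% z-tests.

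Band proportions:
- Mild: Φ((13.5 − 18)/6) = Φ(−0.75) = 22.7%, against Φ((13.5 − 16.092)/6) = Φ(−0.432) = 33.3%. PR 1.47.
- Severe: 1 − Φ((26.5 − 18)/6) = 7.8%, against 1 − Φ((26.5 − 16.092)/6) = 4.1%. PR 0.53.
- Moderate, by subtraction: 69.5% against 62.6%. PR 0.90.
- Score of 14 or more: 77.3% against 66.7%. PR 0.86.

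Mean score: SE = 6 x √(2/340) = 0.460; 1.908/0.460 = 4.15; power = Φ(4.15 − 1.96) = 99%.

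Score of 14 or more: difference 0.106; SE 0.0344 under the null and 0.0342 under the alternative; power = Φ((0.106 − 1.96 x 0.0344)/0.0342) = 87%. The 0-13 band is its complement, so its power is the same.

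| Measure | Power, 10.6% shift | Power, 5.3% shift |
|---|---|---|
| Mean score | 99% | about 55% |
| 14 or more (equally 0-13) | 87% | 33% |
| Severe | 53% | 19% |
| Moderate | 48% | 13% |

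Over control means 14 to 20 and SD 5 to 7, power for the mean is 79% to above 99% at the full shift and 28% to 79% at half. For the moderate band it is 9% to 88% and 5% to 33%.

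**The case against.** The best defence is that three exclusive bands are an ordinary ordinal distribution. A reader who sees all three would recognise mild up, moderate down and severe down as a shift towards lower stress. Nothing in the article says the bands will be pooled. The 0-13 band already carries the contrast at 14, with the same power. Choosing between a mean and categories is partly preference, and an analysis plan that is not shown may name the contrast.

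Much of this stands, and it rules out several stronger readings that a reader might infer:
- That stress prevalence will simply be 100% in both arms. This holds only if the bands are pooled, which the row's title allows but no text states.
- That no band can show benefit. The 0-13 band can, as the complement of 14 or more, with benefit at a ratio above 1. The severe band also has a consistent direction.
- That the three ratios must conflict. In the base case they tell one coherent story; only the moderate band, read alone, is ambiguous.
- That the mediation analysis is damaged. The Statistical analysis section lists stress as a mediator without saying that it is banded.

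The analysis-plan argument does not remove the point. The article states a definition rather than leaving one open, and under that definition a score of 0 is counted as stress. The depression row shows that Table 1 had room for a cut-off.

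**Conclusion.** The point holds for one secondary outcome. As defined, the row yields no single prevalence of stress with a stated direction of benefit: pooled it is a constant, and band by band it is three ratios, one of them without a fixed direction. The coverage result is exact and needs no assumptions.

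The size of the power loss does rest on assumptions. The document gives no score mean or SD, does not tie the 10.6% to this scale or to a mean score, and plans repeated-measures models that the single-visit calculation ignores. Within those limits, the mean score is the most powerful of the measures compared in the base case, and the moderate and severe bands fall well short of it. The primary outcome is untouched.

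**What to change.** In Table 1, and in the analysis plan if it repeats the row:
- Make the outcome the mean Perceived Stress Scale score (0-40, higher meaning more stress), analysed as a mean difference with the Gaussian, identity-link model already in the Statistical analysis section.
- Add one supportive binary outcome, score of 14 or more, with benefit stated as a prevalence ratio below 1. It should not stand alone, since it loses contrast if control scores are high (ratio 0.97 to about 1.00 at control means of 26 to 30).
- Relabel 0-13 as low and present the three bands descriptively by arm.

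The same questionnaire data serve, so nothing new is collected. The cost is a documented change to a listed secondary outcome, which should be made before results are seen.

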### Sample size calculation

The overall trial sample size was determined based on the primary outcome of prevalence of any STH at any follow-up (ages 6, 12, 18, 24 months). We estimated the required sample size using the standard formula for comparisons of two groups with repeated measures of a binary outcome (Liu and Liang 1997). From 2017-2020 in Sirajganj District, prevalence of *Ascaris lumbricoides* was 25.1%, and prevalence of *Trichuris trichiura* was <10% (Gerber et al. 2023). To be conservative, we assumed the prevalence of any STH in the control group over four follow-up rounds would be 20%. In our prior analyses of the association between concrete floors and any STH, the unadjusted prevalence ratio was 0.40 (95% CI 0.28, 0.56) (Benjamin-Chung et al. 2021), and the adjusted prevalence ratio was 0.73 (95% CI 0.52, 1.01) (Benjamin-Chung et al. 2015). We assumed a minimum detectable prevalence ratio of 0.70. We assumed intraclass correlation = 0.066 for repeated measurements of STH prevalence among children < 2 years (Platts-Mills et al. 2015). Assuming a Type I error = 0.05 and Type II error = 0.20, for a two-sided hypothesis test, the required number of households per arm is 336. Inflating this to account for 15% loss to follow-up and 10 households per randomisation block, the total required sample size across both arms is 800. 15% loss to follow-up was assumed based on the findings from the prior trial carried out by our team in rural Bangladesh (Luby et al. 2018), in which 6.5% of pregnant women miscarried or had still births, 3.5% of children died by 12-month follow-up, and <1% died between 12-24 months follow-up.

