### Baseline survey

The study team will administer a baseline survey to record household construction materials, household census, assets, income, animal ownership, WASH infrastructure and practices, demographics, maternal depression, and the illness and activities of a non-index child aged <3 years (index children will be in utero) (Table 2). Surveys will include questions about satisfaction with housing and floor quality. Field staff will visually assess floors for cracks, damage, cleanliness, and the presence of animal feces, food scraps, or trash. Field staff will record participant names and cell phone numbers to assist with tracking should participants relocate during the follow-up period. Field staff will receive standardized training on survey administration and sample collection.

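### Table 1 scores three grades of maternal satisfaction as one answer; comparing the graded answer alongside would cheaply recover power if most control mothers are already satisfied

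*Protocol article*

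**What the plan says.** Table 1 (Maternal outcomes) has two rows on the same three items: quality of life, floor quality and housing quality.

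- The level row is the "Proportion of mothers reporting that they were “very satisfied”, “satisfied”, or “somewhat satisfied” with their quality of life", and the same for the other two items, at each follow-up.
- The change row is the "Proportion of mothers with an improvement in their reported quality of life, household floor quality and housing quality between baseline and each follow-up".

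Both are proportions. For repeated secondary outcomes the Statistical analysis section plans generalized estimating equations, with "prevalence ratios for binary outcomes using a log link and binomial family". All models condition on geographic block and use robust standard errors.

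The graded answers are collected before and after the intervention. The Baseline survey section states: "Surveys will include questions about satisfaction with housing and floor quality". Table 2 marks quality of life and satisfaction with housing at baseline. It then marks housing satisfaction at 6, 12, 18 and 24 months and quality of life at 3, 12 and 24 months. Household surveys cover the full sample of 800.

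The article gives no number of grades, control prevalence, target effect or power for satisfaction. Its only satisfaction figure comes from a prior study in Mexico: "18.7% higher satisfaction with quality of life among mothers".

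**The concern.** The level row takes an ordered answer with at least three positive grades and cuts it below the lowest of them. Two things follow from the definition alone.

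1. A mother who would answer 'somewhat satisfied' on a soil floor and answers 'very satisfied' on concrete adds nothing to the arm difference in this row.
2. If a share p of control mothers is satisfied to any degree, the prevalence ratio cannot exceed 1/p.

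The Introduction gives quality of life as one reason to expect benefit, and the Statistical analysis section lists it as a mediator in the maternal pathway. If most control mothers already give some positive answer, a modest real shift could be reported as little or no difference in the level row because of where the scale was cut.

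**Working it through.** **Inputs from the article.** 800 households randomised 1:1 gives 400 per arm, and 15% loss leaves 400 × 0.85 = 340. Error rates are stated for the primary outcome only ("Assuming a Type I error = 0.05 and Type II error = 0.20, for a two-sided hypothesis test"); the two-sided 5% level is carried over. There is no stated power for satisfaction to reproduce.

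**Assumptions (not in the article).** Six grades, three negative and three positive; one visit; a common odds ratio (OR) across all cut points. Control distributions from lowest to highest grade:

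- 50% satisfied: .10/.15/.25/.25/.20/.05
- 65%: .05/.10/.20/.30/.28/.07
- 80%: .03/.05/.12/.30/.38/.12
- 90%: .01/.03/.06/.30/.42/.18
- 95%: .005/.015/.03/.25/.45/.25

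**Ceiling.** The largest possible ratio 1/p is 2.00 at 50% satisfied, 1.25 at 80%, 1.11 at 90% and 1.05 at 95%. If the cited 18.7% is read as a prevalence ratio of 1.187, it becomes impossible once p exceeds 1/1.187 = 84%.

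**Power formulas.**

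- Planned: power = Φ(ln(q/p)/SE − 1.96), with SE² = (1−p)/(np) + (1−q)/(nq), where q is the satisfied share under intervention.
- Graded: power = Φ((θ − 0.5)/SE − 1.96), with SE² = [(1 − Σ p̄³)/12] × (2n/n²). Here θ is the chance that an intervention mother answers higher than a control mother, ties counted half, and p̄ is the mean share in each grade.

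**Worked case: 80% satisfied, OR 1.5.** Intervention odds are 1.5 × 4 = 6, so q = 6/7 = 0.857 and the ratio is 1.071. SE = √(0.2/272 + 0.143/291.4) = 0.0350, so ln(1.071)/SE = 1.97 and power is Φ(0.01) ≈ 50%. For the graded answer θ = 0.561 and SE = √(0.9076/12 × 680/115600) = 0.0211, so z = 2.89 and power is Φ(0.93) ≈ 82%.

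**All cases at OR 1.5.**

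| Controls satisfied | Prevalence ratio | Graded answer | Loss (points) |
|---|---|---|---|
| 50% | 74% | 84% | 10 |
| 65% | 68% | 84% | 16 |
| 80% | 50% | 82% | 32 |
| 90% | 31% | 82% | about 50 |
| 95% | 18% | 81% | 63 |

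A simulation with the positive grades evenly spread agrees: graded against binary, 84.5% against 73.7% at 50% satisfied, 84.6% against 50.7% at 80%, and 81.6% against 30.9% at 90%.

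**Sensitivity.**

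- *Larger shifts.* At OR 2 the loss is 1–2 points at 50–65% satisfied, about 11 at 80% and about 36 at 90%. At OR 3 it is about zero up to 80%.
- *Fixed ratio of 1.187.* The loss is 11 points at 50% satisfied, 9 at 60%, 2 at 70% and 0 at 80%. Holding the ratio fixed implies ever larger shifts: 0.80 × 1.187 = 0.95, an odds ratio of about 4.7.
- *Pooled visits.* Assume four visits and a within-mother correlation of 0.3. The effective number per arm is 340 × 4/(1 + 3 × 0.3) = 716. At OR 1.5 binary power is then about 97%, 94% and 82% at 50%, 65% and 80% satisfied, and the loss is about 2, 5 and 17 points. It stays above 40 at 90% or more.
- *The improvement row.* At OR 1.5, with an assumed moderate correlation between baseline and follow-up answers (0.3 to 0.5), its power is roughly 43–62%. That beats the level row at high control prevalence but stays below the 81–84% of the graded comparison.

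**The case against.** The strongest objection is that a reader might infer the trial cannot see movement among satisfied mothers. The article does not support that. The improvement row is a separate pre-specified outcome on the same items, and a move from 'somewhat' to 'very satisfied' can count there. What remains is that this row is also binary, does not say how large an improvement must be, merges worsening with no change, and cannot register a mother already at the top grade at baseline.

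A reader might also infer that the ratio will hit its ceiling, or that a fixed 10 to 50 points of power is lost. Neither follows. The ceiling matters only if control prevalence is high, and the article gives none. Control households keep soil floors, so satisfaction with the floor, and perhaps with housing, could be low. Every power figure rests on an assumed scale, distribution and odds ratio, and mostly on a single visit where the plan pools visits.

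Finally, percent satisfied is interpretable and pre-specified, nothing here is contradictory, and an analysis plan not shown may already add a graded comparison. This is fair. It argues for keeping the prevalence ratio, not against adding to it: the cut and the effect measure are both fixed in the article, and no graded comparison is stated.

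**Conclusion.** The point stands as a cheap improvement to one secondary outcome; the primary conclusion is unaffected. It is certain that the level row ignores shifts among the three positive grades and that its ratio is capped at 1/p. The size of the loss is conditional. With six grades, OR 1.5, 340 mothers per arm and one visit, it is about 10 points at 50% of controls satisfied, 32 at 80% and 50 at 90%. It is near zero for large shifts at moderate prevalence, and at OR 1.5 with up to 90% satisfied it shrinks when visits are pooled. Overall quality of life is the item most plausibly affected, and floor satisfaction may not be affected at all. Since control prevalence is unknown, the useful property of the graded comparison is that its power at OR 1.5 hardly depends on it.

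**What to change.** Keep the three-grade prevalence ratio as the interpretable summary. Beside it, pre-specify a between-arm comparison of the full ordered answer at the visits where each item is collected, with the mother's baseline answer as covariate, and show the full distribution of answers by arm. Because Tables 1 and 2 list different visits for quality of life, name those visits explicitly.

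The method must cope with 800/10 = 80 blocks of about 8 mothers each after losses. Three options are suitable:

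- a block-conditioned mean difference in the graded score with the planned robust standard errors, which is closest to the models already planned for continuous outcomes;
- a block-stratified rank test, which would need a separate step to use the baseline answer;
- a proportional-odds model with blocks as random effects.

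A proportional-odds model with some 80 fixed block indicators should be avoided, because sparse strata can push the estimate away from the null. A small simulation (38 runs, 80 blocks of 8) gave a mean log odds ratio of 0.47, standard error 0.03, against a true 0.405.

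The cost is analysis wording only: one more analysis per item, and a graded score or odds ratio that is less familiar than a prevalence ratio. It should be fixed before unblinding, so that it is not a post hoc choice.
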